### Eligibility criteria

2.3

Healthy men aged from 18 to 35 years with no history of musculoskeletal injury in the hip and knee regions in the 2 months before the study who do not regularly use pharmacological agents and/or nutritional supplements and who complete at least 80% study procedures will be included in the study. Volunteers who show any musculoskeletal injury in the 2 months before the study or who become injured during the study, who regularly use any type of nutritional supplement of pharmacological agent, or who show signs and symptoms of any neurological, metabolic, inflammatory, pulmonary, oncological, or cardiovascular disease that may limit the execution of high-intensity exercises will be excluded from the study.

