### Subjects and sample size

2.2

As no studies assessing the effects of PBMT during the detraining period after an aerobic training program are currently available, the number of participants per group in the present study was calculated based on a pilot study, with 5 volunteers per group, which was conducted by our research group in order to estimate the sample size. A β value of 20% and an α of 5% were used to calculate the sample size.

The pilot study showed that applying PBMT during the detraining period resulted in a time to exhaustion (primary outcome of this study) of 923.60 seconds (65.77 standard deviation) during the progressive treadmill test, whereas applying the placebo during the detraining period resulted in a time to exhaustion of 846.82 seconds (99.23 standard deviation). We used the Researcher's Toolkit to calculate the sample (https://www.dssresearch.com/KnowledgeCenter/toolkitcalculators/samplesizecalculators.aspx).

On the basis of the aforementioned parameters used to calculate the sample, we found 15 volunteers per group, for a total of 60 volunteers. Therefore, predicting a 20% sample loss, 72 healthy, physically inactive male volunteers aged from 18 to 35 years will be recruited for the study to ensure a final sample size of 60 volunteers. As the PBMT device used in the study causes no harmful thermal effects,^[23]^ volunteers of different skin colors will be recruited.

Volunteers will be informed about all study procedures and will be asked to sign the Informed Consent Form before their enrollment in the study.

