### Randomization and blinding and experimental groups

2.4

To avoid selection bias and to ensure that all individuals are randomly allocated to any group, balanced block randomization will be performed based on the primary outcome (time to exhaustion in the progressive treadmill test) by a researcher who will have no contact with the study subjects or the other researchers involved in the project.

A researcher will program the device (PMBT or placebo) and will be instructed not to inform the volunteers or other researchers as to the type of treatment (PMBT or placebo). Therefore, the researcher responsible for the treatment will be blinded to the type of treatment being administered to the volunteers. The sounds and signals emitted from the device as well as the information displayed on the screen will be identical, regardless of the type of treatment (PMBT or placebo).

Randomization labels will be created through the random.org website, and a series of sealed, opaque, and numbered envelopes will be used to ensure confidentiality and will determine to which experimental group each volunteer will be allocated. Volunteers will be allocated as described below:

**A**: PBMT before and after the aerobic training sessions (12 weeks, 3 times a week) and PBMT during the detraining period (4 weeks, 3 times a week).**B:** PBMT before and after the aerobic training sessions (12 weeks, 3 times a week) and placebo during the detraining period (4 weeks, 3 times a week).**C:** Placebo before and after the aerobic training sessions (12 weeks, 3 times a week) and PBMT during the detraining period (4 weeks, 3 times a week).**D:** Placebo before and after the aerobic training sessions (12 weeks, 3 times a week) and placebo during the detraining period (4 weeks, 3 times a week).

The individuals randomly allocated to the different groups will be subjected to 12 consecutive weeks of aerobic endurance training in a motorized treadmill, with 3 training sessions per week on nonconsecutive days.

After the 12-week training period, the volunteers will receive the treatment, either PBMT or placebo, depending on the group to which they were allocated, during 4 weeks (3 times a week) without training.

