The evaluations described below will be performed before starting the protocol (baseline) and after 4, 8, and 12 weeks of aerobic endurance training, as well as after 4 weeks without training (detraining period) at 16th week. A flowchart summarizing the procedures of this study is presented in Fig. 1.

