#### Cardiorespiratory evaluation

2.2.1

Ergospirometry is currently the most accurate cardiorespiratory fitness test.^[24]^ In this study, we will use a progressive treadmill protocol, previously used by our research group,^[5,7,17]^ an ergometric treadmill model Super ATL, and a gas analyzer model VO2000 (Inbrasport, Porto Alegre - RS, Brazil), which will be connected to a microcomputer for data visualization and recording. The ergospirometry test will start with the treadmill set at 1% slope, with an initial speed of 3 km/h, which will be maintained until the end of the warm-up phase lasting 3 minutes. After the warm-up phase, the speed will be increased by 1 km/h every minute until reaching a maximum speed of 16 km/h. The end of the test will be defined by the volunteers, who will be instructed to perform the test until they reach exhaustion.^[5,7,17]^ Then, the recovery phase will begin, lasting 3 minutes at a speed of 6 km/h. In the test, data on the total time of the exercise (time to exhaustion), maximum oxygen uptake in relative values in relation to body mass (VO_2max_), and aerobic and anaerobic thresholds will be recorded.^[5,7,17]^ These data will be used to assess the performance of the subjects in the exercise protocol, as they are currently the parameters most used for this purpose in the literature.^[24]^

The entire test will be monitored by electrocardiography and blood pressure measurements. If any abnormal changes in heart rate or in blood pressure are found or if the volunteer has any complaint, the test will be discontinued and the volunteer will be excluded from the study.

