### Statistical analysis

2.6

The primary outcome will be time until exhaustion obtained from progressive treadmill test. The secondary outcomes are VO_2max_ and fat percentage test. The intention-to-treat analysis will be followed a priori. All the data will be analyzed by a blinder researcher not involved in data collection. The findings will be tested for their normality using the Shapiro–Wilk test. Parametric data will be expressed as mean and standard deviation and nonparametric data as median and respective upper and lower limits. Parametric data will be analyzed by 2-way repeated measures analysis of variance (ANOVA; time vs experimental group) with post-hoc Bonferroni correction. Nonparametric data will be analyzed using the Friedman test and, secondarily, the Wilcoxon signed-rank test. Data will be analyzed in terms of both their absolute values and their percentage of change based on the values established in the baseline. The significance level will be set at *P* < .05.

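### The 80% completion rule contradicts the stated intention-to-treat analysis, and the injury and exercise-test exclusions do so too if excluded means removed from the analysis

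*Protocol article*

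**What the plan says.** Section 2.6 (Statistical analysis) makes the only statement about who is analysed: "The intention-to-treat analysis will be followed a priori".

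Three other rules bear on who remains in the trial:

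- Section 2.3 (Eligibility criteria) lists, alongside age and injury history, that men "who complete at least 80% study procedures will be included in the study".
- The same section lists among its exclusions men "or who become injured during the study".
- The Cardiorespiratory evaluation section covers abnormal changes in heart rate or blood pressure as well as complaints: "if the volunteer has any complaint, the test will be discontinued and the volunteer will be excluded from the study".

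On timing, section 2.4 says that "balanced block randomization will be performed based on the primary outcome (time to exhaustion in the progressive treadmill test"), so allocation presumably follows the baseline test. The evaluations are then repeated "after 4, 8, and 12 weeks of aerobic endurance training, as well as after 4 weeks without training".

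The article does not say whether men caught by these rules are followed up or kept in the analysis.

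**The concern.** Intention-to-treat means that every randomized man counts in the group to which he was allocated. Completing 80% of procedures, and becoming injured along the way, are facts about what happens during the 16 weeks after allocation. A rule that admits men on the first of these selects the sample on a post-randomization event.

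The article credits the intervention with faster recovery and longer time to exhaustion. Adherence, injury and tolerance of a maximal test could therefore respond to treatment and be related to the primary outcome. If they did, dropping the affected men would undo the balance that randomization gave, in either direction, and the result could not be described as intention-to-treat.

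**Working it through.** **1. The rules side by side**

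| Rule | When it can be known | Compatible with section 2.6? |
|---|---|---|
| At least 80% of procedures completed (2.3) | Only after allocation | No: it is worded as a condition of being included |
| Injured during the study (2.3) | During the study | Only if exclusion means stopping procedures |
| Abnormal heart rate or blood pressure change, or any complaint, in a test (Cardiorespiratory evaluation) | Baseline, weeks 4, 8, 12 and 16 | Baseline: yes, ordinary screening. The other four: only if exclusion means stopping procedures |

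**2. The plan's own figures (section 2.2)**

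Inputs: pilot means 923.60 s (SD 65.77) and 846.82 s (SD 99.23); α 5%, β 20%; 15 per group, 60 in total; 72 recruited for a 20% loss.

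- Difference: 923.60 − 846.82 = 76.78 s.
- Pooled SD: √[(65.77² + 99.23²)/2] = 84.18 s.
- n per group = 2 × [84.18 × (z_α + 0.842)/76.78]². With z_α = 1.645 (one-sided) this is 14.86, so 15, which reproduces the plan. With z_α = 1.960 (two-sided) it is 18.87, so 19. The article does not state sidedness; that is a separate matter.
- Loss planned for: 72 − 60 = 12 men (16.7%), or 0.20 × 72 = 14.4 men at the stated rate. This is loss from any cause and is not attributed to these rules.

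**3. How large a bias could be (assumed scenarios)**

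Assume no true effect, outcome SD 84.18 s, and exclusion of the lowest fraction p of an arm on a normal tendency that correlates ρ with the outcome. The retained men's mean then rises by ρ × 84.18 × k(p), where k(p) = φ(z_p)/(1 − p), z_p is the p-quantile of the standard normal and φ its density. The bias is ρ × 84.18 × [k(p₂) − k(p₁)]. The exclusion rates are chosen to average 16.7%.

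| Excluded, arm 1 / arm 2 | k(p₁), k(p₂) | ρ = 0.3 | ρ = 0.5 | ρ = 0.7 |
|---|---|---|---|---|
| 16.7% / 16.7% | 0.300, 0.300 | 0 s | 0 s | 0 s |
| 10% / 23.3% | 0.195, 0.399 | 5.2 s | 8.6 s | 12.0 s |
| 5% / 28.3% | 0.109, 0.472 | 9.2 s | 15.3 s | 21.4 s |

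With ρ = 0 the bias is 0 s in every row. As a share of 76.78 s, the second row is 7% to 16% and the third 12% to 28%. With 15 per group analysed, the standard error of a difference is 84.18 × √(2/15) = 30.7 s. The nominal two-sided 5% error then becomes about 0.053 to 0.068 in the second row and 0.060 to 0.107 in the third.

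The sign depends on which arm loses more men. If low performers are removed more often from placebo, the placebo mean rises and a benefit is hidden; the reverse pattern favours PBMT.

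**4. Size of the analysis set**

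Keeping all randomized men gives 72/4 = 18 per group instead of 15. Normal-approximation power for the pilot difference is then 0.86 against 0.80 (one-sided), or 0.78 against 0.70 (two-sided). This holds only if outcomes are obtained for everyone and the effect is not diluted.

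**The case against.** The strongest reply is that section 2.6 is the only place that defines the analysis, and it says intention-to-treat. Excluding a man from the study for injury or a test finding may mean only that he stops procedures, and handling of his data is commonly left to a fuller document. That stands for the injury and test rules. It does not rescue the 80% rule, which is written as a condition of inclusion.

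Blinding is a second reply. Volunteers, therapists and assessors are blinded and the device gives identical signals, so exclusion decisions should not follow knowledge of allocation. That also stands: differential exclusion would need a real treatment effect on adherence, injury or tolerance. The article's claims for the intervention make this possible, but it gives no evidence of it.

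Third, the calculation compares means at one time point, while the plan also analyses percentage change from baseline. If excluded men were already slower at baseline, part of the bias would cancel there.

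A reader might infer that the analysis will contain only completers without injury or complaint, that all five tests act after allocation, or that a material bias is to be expected. The article supports none of these: it never says that such men leave the analysis set, the baseline test appears to precede allocation, and equal exclusion across arms gives a bias of about zero.

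**Conclusion.** The contradiction between the 80% completion rule and the intention-to-treat commitment is on the face of the article and does not depend on any calculation. Followed as written, section 2.3 gives a completer-type set. The injury and test rules are ambiguous, and contradict section 2.6 only on the reading that excluded men leave the analysis.

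The possible bias runs from about 0 s to about 21 s, up to 28% of the pilot difference. This range rests on assumed exclusion rates and correlations; the documents fix neither size nor direction. A later analysis plan cannot satisfy both sections as they stand, so the correction belongs in the protocol.

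**What to change.** - In section 2.3, remove the 80% completion rule and in-study injury as conditions for membership of the analysis set.
- In section 2.6, state that every randomized volunteer is analysed in his allocated group with all data obtained, whatever his adherence, injury or early test termination.
- Use the 80% rule only to define a per-protocol sensitivity set.
- Reconcile section 2.3, the Cardiorespiratory evaluation section and section 2.6 so that exclusion refers to stopping study procedures and not to removal from the analysis. The safety stopping rules, and any decision on further testing of a man who has been stopped, remain unchanged and with the investigators.

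The cost is amendment wording. The intention-to-treat estimate may be diluted by non-adherence, and men who stop early will have missing later visits, possibly including week 16, which the analysis must accommodate.

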### Randomization and blinding and experimental groups

2.4

To avoid selection bias and to ensure that all individuals are randomly allocated to any group, balanced block randomization will be performed based on the primary outcome (time to exhaustion in the progressive treadmill test) by a researcher who will have no contact with the study subjects or the other researchers involved in the project.

A researcher will program the device (PMBT or placebo) and will be instructed not to inform the volunteers or other researchers as to the type of treatment (PMBT or placebo). Therefore, the researcher responsible for the treatment will be blinded to the type of treatment being administered to the volunteers. The sounds and signals emitted from the device as well as the information displayed on the screen will be identical, regardless of the type of treatment (PMBT or placebo).

Randomization labels will be created through the random.org website, and a series of sealed, opaque, and numbered envelopes will be used to ensure confidentiality and will determine to which experimental group each volunteer will be allocated. Volunteers will be allocated as described below:

**A**: PBMT before and after the aerobic training sessions (12 weeks, 3 times a week) and PBMT during the detraining period (4 weeks, 3 times a week).**B:** PBMT before and after the aerobic training sessions (12 weeks, 3 times a week) and placebo during the detraining period (4 weeks, 3 times a week).**C:** Placebo before and after the aerobic training sessions (12 weeks, 3 times a week) and PBMT during the detraining period (4 weeks, 3 times a week).**D:** Placebo before and after the aerobic training sessions (12 weeks, 3 times a week) and placebo during the detraining period (4 weeks, 3 times a week).

The individuals randomly allocated to the different groups will be subjected to 12 consecutive weeks of aerobic endurance training in a motorized treadmill, with 3 training sessions per week on nonconsecutive days.

After the 12-week training period, the volunteers will receive the treatment, either PBMT or placebo, depending on the group to which they were allocated, during 4 weeks (3 times a week) without training.

The evaluations described below will be performed before starting the protocol (baseline) and after 4, 8, and 12 weeks of aerobic endurance training, as well as after 4 weeks without training (detraining period) at 16th week. A flowchart summarizing the procedures of this study is presented in Fig. 1.

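### Allocation is balanced on baseline time to exhaustion but the analysis does not adjust for it, so comparisons of absolute values at a visit lose power

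*Protocol article*

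**What the plan says.** On allocation, section 2.4 of the Protocol article states: "balanced block randomization will be performed based on the primary outcome (time to exhaustion in the progressive treadmill test". On timing, the same section states: "The evaluations described below will be performed before starting the protocol (baseline) and after 4, 8, and 12 weeks of aerobic endurance training", with a last evaluation at week 16. The balancing variable is therefore the week-0 value of the primary endpoint (section 2.6: "The primary outcome will be time until exhaustion obtained from progressive treadmill test").

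On analysis, section 2.6 states: "Parametric data will be analyzed by 2-way repeated measures analysis of variance (ANOVA; time vs experimental group) with post-hoc Bonferroni correction". Baseline enters in one other way: "Data will be analyzed in terms of both their absolute values and their percentage of change based on the values established in the baseline". Neither baseline nor the randomisation block is named as a term in any model. Because the article itself fixes the model, this is not a detail left to a separate analysis plan.

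The article does not give the block size, how baseline values define the blocks, the correlation between baseline and later values, or the error term for the post-hoc comparisons.

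**The concern.** Balancing on a prognostic baseline value removes much of its variation from the difference between group means. If the analysis leaves baseline out, that variation stays in the error term. The estimated standard error then exceeds the true one, and the precision gained by balancing does not reach the test.

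Treating baseline as a level of time does not adjust for it. It makes the group-by-time interaction a change-type comparison and averages an untreated visit into the group main effect. Percentage change uses baseline, but it is not covariate adjustment either.

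What is at stake is power, in a four-arm trial with 15 per arm and Bonferroni correction.

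**Working it through.** **Inputs from section 2.2.** Pilot means 923.60 s and 846.82 s, SDs 65.77 and 99.23, 15 per group, and "A β value of 20% and an α of 5% were used to calculate the sample size".

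- Difference: 923.60 − 846.82 = 76.78 s.
- Pooled SD: √[(65.77² + 99.23²)/2] = 84.18 s.
- Effect size: 76.78/84.18 = 0.912 SD.

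**The plan's own figure.** n = 2(z_α + z_β)² × 84.18²/76.78². One-sided α of 5% gives 14.86, so 15, which matches the article. Two-sided gives 18.87, so 19. Two-sided 5% is used below.

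**Assumptions.** The correlation r is not in the article; 0.3 to 0.9 is shown. Close balance on baseline, equal variances, and one pairwise comparison at one visit without Bonferroni correction.

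**Variance of the group difference, in units of 2σ²/n.**
- True variance under close balance: 1 − r².
- Variance used by the unadjusted test of visit values: 1, too large by 1/(1 − r²), which is 1.33 at r = 0.5 and 1.96 at r = 0.7.
- Variance used by a change-score test: 2(1 − r), too large by 2/(1 + r), which is 1.33 and 1.18.

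**Type I error, visit values.** 2[1 − Φ(1.96/√(1 − r²))].
- r = 0.5: 1.96/0.866 = 2.263, giving 2.4%.
- r = 0.7: 1.96/0.714 = 2.745, giving 0.6%.

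**Power.** The standardised effect is 0.912/√(2/15) = 2.498.
- Unadjusted values: Φ[(2.498 − 1.96)/√(1 − r²)].
- Change score: Φ[(2.498 − 1.96√(2(1 − r)))/√(1 − r²)].
- Adjusted: Φ[2.498/√(1 − r²) − 1.96].

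| r | Values | Change | Adjusted |
|---|---|---|---|
| 0.3 | 71% | 57% | 75% |
| 0.5 | 73% | 73% | 82% |
| 0.7 | 77% | 92% | 94% |
| 0.9 | 89% | about 100% | about 100% |

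**Simulation check.** With 15 per arm, 0.91 SD and rank-ordered blocks, at r = 0.5 and 0.7:
- type I error for values is 2.7% and 0.7%;
- power is 71% and 74% for values, 70% and 91% for change, 81% and 93% adjusted.

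**Dependence on the blocking.** Type I error of the four-group test of week-16 values (2,500 simulated trials per cell, equal correlation between visits), at r = 0.5 and 0.7:
- rank-ordered blocks: 1.8% and 0.4%;
- two baseline strata: 2.8% and 1.1%;
- no stratification: about 5%.

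The power gain from adjustment does not need tight blocks. For the same four-group test at r = 0.5 it was 82% against 92% with no stratification, 84% against 93% with two strata, and 85% against 93% with rank-ordered blocks.

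**Dependence on the error term.** Suppose the post-hoc test instead uses the pooled within-subject residual, proportional to 1 − r. The true variance then exceeds the one used by (1 − r²)/(1 − r) = 1 + r. At r = 0.5, 1.96/√1.5 = 1.600, giving 11%. At r = 0.7, 1.96/√1.7 = 1.503, giving 13%. That is anti-conservative.

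**The case against.** The strongest reply is that the plan does use baseline. It commits to percentage change as well as absolute values, and the group-by-time interaction is a change-type test. If baseline and outcome are strongly correlated, these lose little: 91% against 93% at r = 0.7 for a simple change score. This stands, and it limits the material loss for change-based tests to correlations of about 0.5 or below. It does not help the analysis of absolute values. A simple change score is also only a stand-in here for percentage change, which was not simulated.

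Second, rank-ordered blocks are the tightest case. They would need every baseline value before anyone is allocated, and the article describes only balanced blocks and numbered envelopes. This stands too: with coarser balance the type I error moves back towards 5%. The loss of power against an adjusted analysis remains.

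Third, a reader might infer that all between-group tests in the plan are too conservative. The documents do not support that. The post-hoc error term is not stated, and the pooled within-subject residual would give 11% to 13% type I error. The interaction test rejected a true null 4.6% to 6.1% of the time under rank-ordered blocks when correlation decayed over time and no sphericity correction was made.

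**Conclusion.** The mismatch is in the text: allocation uses baseline time to exhaustion and the stated model does not adjust for it. For absolute values compared with the between-subject error at a visit, standard errors are too large and power is lost, about 10 percentage points at r = 0.5 (71% against 81%) and 19 at r = 0.7 (74% against 93%). These figures assume 15 analysed per arm, 0.91 SD, rank-ordered blocks and a single two-sided 5% test. The blocking and the correlation are assumptions, so the direction for this test is firmer than the size.

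Two stronger readings should be avoided. The precision from balancing is not wholly discarded, because the change-based analyses recover much of it at high correlation. Nor does this point show bias or an excess of false positives for the visit-wise test, whose error is conservative. It is an efficiency weakness that should be corrected, not a flaw that invalidates the trial.

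**What to change.** Adjust between-group comparisons of time to exhaustion for its baseline value, in one of two ways:

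- a repeated-measures model of the post-baseline visits, with baseline and a baseline-by-time term as covariates; or
- a constrained longitudinal model that keeps baseline as a level of time and sets the group means equal there.

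Taking baseline out of the time factor is thus one option, not a requirement. Make the adjusted model the primary between-group analysis in place of unadjusted absolute values and percentage change. A covariate cannot enter the planned Friedman and Wilcoxon tests, so adjustment has to come through the model.

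Adjusting VO2max and fat percentage for their own baselines would bring a similar gain in precision. It does not follow from the randomisation scheme, which balances only on time to exhaustion.

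The cost is slightly more model specification. No new data or participants are needed.

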Various clinical training methods and protocols for performance enhancement, health promotion, and rehabilitation are used by different groups, including athletes, physically active individuals, sedentary individuals, and patients with different disorders and diseases. Among the training types and protocols, aerobic endurance training stands out. However, training protocols very often require discontinuation due to illness, injury, or other factors that may alter the capacity for physical activity, thereby causing a rapid loss of aerobic endurance conditioning,^[21]^ which represents a challenging problem in clinical practice. It should also be noted that, thus far, no evidence or consensus on any particular resource or method that may decrease the effects of detraining has been found.

An interesting study conducted by Wasik et al^[22]^ assessed the effects of PBMT on the oxidative metabolism of peripheral blood cells (erythrocytes, granulocytes, and lymphocytes) by irradiating heparinized blood samples from 15 volunteers. After irradiation, partial pressure of oxygen (PO_2_) and oxygen saturation (SaO_2_) increased, which shows that PBMT-induced photochemical reactions in blood cells may enhance the oxygen-carrying ability of blood. These interesting findings suggest that PBMT may attenuate the loss of performance observed during the detraining period after an aerobic endurance training program because oxygen transport and, consequently, the ability of muscles to use it, decrease during the detraining period.

Therefore, the effects of PBMT on aerobic endurance detraining remain unknown and it is a scientific challenge that will represent a key advance in the knowledge of this field when it is overcome. With this aspect in mind, this project aims to assess the ergogenic effects of PBMT during the detraining period after completing an aerobic endurance training protocol.

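### The detraining treatment is allocated before training although it is not needed until week 12, so the intention-to-treat set includes men who never start it and balance rests on untrained fitness

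*Protocol article*

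**What the plan says.** The aim, at the end of the Introduction, is to "assess the ergogenic effects of PBMT during the detraining period after completing an aerobic endurance training protocol". The sample size (section 2.2) rests on the same contrast, using pilot times to exhaustion with PBMT and with placebo during detraining.

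Section 2.4 describes one allocation by sealed envelope to arms A to D, and then: "The individuals randomly allocated to the different groups will be subjected to 12 consecutive weeks of aerobic endurance training in a motorized treadmill". The later treatment follows from that same allocation: "After the 12-week training period, the volunteers will receive the treatment, either PBMT or placebo, depending on the group to which they were allocated". By the arm definitions, A and B both receive PBMT throughout training, and C and D both receive placebo. Within each pair only weeks 12 to 16 differ.

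On balance, section 2.4 says "balanced block randomization will be performed based on the primary outcome (time to exhaustion in the progressive treadmill test". Tests are scheduled at baseline and at weeks 4, 8, 12 and 16, so a week-12 value will exist, but no role in allocation is given to it.

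On loss, section 2.2 recruits 72 men to end with 60, "predicting a 20% sample loss". Section 2.3 excludes men injured during the study and requires completion of at least 80% of procedures. Section 2.6 nevertheless commits to intention to treat, and takes percentage change from baseline.

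**The concern.** Nothing in the design needs the detraining treatment to be fixed before week 12. Fixing it earlier has two consequences.

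- **Analysis set.** Men who leave or are excluded during the 12 training weeks are already counted under a detraining treatment they never receive. Intention to treat keeps them and dilutes the contrast. Leaving them out breaks the stated rule.
- **Balance.** The groups are balanced on time to exhaustion in untrained men. The detraining comparison starts from the trained level, which the baseline value predicts only in part.

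At stake are the power and the clean interpretation of the trial's main comparison.

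**Working it through.** **Inputs from the protocol (section 2.2).** Pilot means 923.60 s and 846.82 s, a difference of 76.78 s; SDs 65.77 s and 99.23 s; alpha 5%, power 80%; 15 per group, 60 in total, 72 recruited (18 per arm).

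**Assumptions.** The share of the 20% loss that falls in training is not given, so 5% to 20% is shown. Men who never start detraining treatment contribute no effect. The pilot SD stands in for the week-12 SD. The balancing method is taken as stratification at the median. The week-0 to week-12 correlation r is 0.5 to 0.8.

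**The plan's own figure.** Root-mean-square SD = √((65.77² + 99.23²)/2) = 84.18 s. Then n = 2(z_α + z_β)² × 84.18²/76.78². A one-sided 5% alpha gives 14.86, so 15 per group, as stated; two-sided gives 18.87, so 19. The 72 is 60 × 1.2. The sidedness is a separate matter.

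**Power (two-sided t test, one pair such as A versus B).** Let L be the proportion lost in training.

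- Week-0 allocation, intention to treat: 18 per arm, difference 76.78 × (1 − L), standard error 84.18 × √(2/18) = 28.06 s.
- Week-12 allocation: 18 × (1 − L) per arm, full difference 76.78 s.

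| Training loss L | Diluted difference | Power, week-0 allocation | Men per arm at week 12 | Power, week-12 allocation |
|---|---|---|---|---|
| 5% | 72.94 s | 0.71 | 17.1 | 0.73 |
| 10% | 69.10 s | 0.67 | 16.2 | 0.71 |
| 15% | 65.26 s | 0.62 | 15.3 | 0.68 |
| 20% | 61.42 s | 0.57 | 14.4 | 0.66 |

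The normal approximation gives 0.74 and 0.76 at 5%, and 0.59 and 0.69 at 20%. The gap arises because dilution multiplies the signal-to-noise ratio by (1 − L), while having fewer men multiplies it by √(1 − L).

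**Balance at week 12 (arms of 15).** With no balancing, the standard error of the chance difference is 84.18 × √(2/15) = 30.7 s. Stratifying a normal variable at its median removes 2/π = 64% of its variance, so balancing on a value with correlation r leaves 30.7 × √(1 − 0.637r²):

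- balanced on week 0, r = 0.5: 28.2 s
- balanced on week 0, r = 0.8: 23.7 s
- balanced on week 12 (r = 1): 18.5 s

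**Does early allocation bias the comparison?** In a simulation of A versus B among men reaching week 12 (assumed week-12 to week-16 correlation 0.8), week-0 allocation gave no bias and a type I error of about 5%, even when loss depended on week-12 fitness. Without adjustment, power among these men was 0.66 with early and 0.65 with late simple allocation. Adjusting week 16 for week 12 raised it to about 0.97 under either timing.

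**The case against.** The strongest reply is that a single allocation to a treatment sequence is a valid design. Within each pair treatment is identical and blinded until week 12, so loss in training cannot depend on the detraining allocation except by chance, and those who remain in A and B stay exchangeable. This stands. A reader might infer that 12 weeks of dropout bias the detraining contrast, or that fitness drifts apart systematically between its arms. The documents support neither: a systematic difference at week 12 is to be expected only between the PBMT-trained and placebo-trained pairs, which is part of the design.

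A reader might also worry about unequal numbers. This is immaterial: groups of 29 and 32 have a standard error only 0.1% above that of the most even split, 30 and 31.

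The chance week-12 difference is ordinary sampling variation, already covered by the significance level, and it is smaller if the trial is read as two pooled halves: 84.18 × √(2/30) = 21.7 s without balancing. Most of the precision comes from using the week-12 value in the analysis, whenever the envelopes are opened. This too stands. The planned time-by-group ANOVA uses within-person change, but section 2.6 states no adjustment for week 12 and takes percentage change from baseline.

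The reply does not remove the conflict over the analysis set. Adjustment for week 12 does nothing for men who have no week-12 value and never start the treatment, yet intention to treat still counts them. The exclusions in section 2.3 sharpen that conflict and are a defect in their own right.

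**Conclusion.** The point holds as a weakness in efficiency and in the definition of the analysis set, not as a bias. One allocation before training makes the intention-to-treat set for the detraining question larger than the set of men who can receive the detraining treatment. The cost in two-sided power is about 0.02 if 5% are lost in training and 0.09 if the whole 20% is lost there. Balancing on the untrained value leaves a chance week-12 difference of about 24 to 28 s instead of 18.5 s (standard errors).

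These figures depend on the assumed timing of loss, no effect in non-starters, the pilot SD, the correlation range and median stratification. That allocation precedes training is read from the order of events in section 2.4; the flowchart is not available here. The change is worth making because it is cheap, not because the present design is invalid.

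**What to change.** 1. At week 0, allocate training-phase PBMT or placebo 1:1, balanced on baseline time to exhaustion.
2. After the scheduled week-12 test, allocate detraining PBMT or placebo 1:1 within each training arm, balanced on week-12 time to exhaustion. Use the same independent researcher, sealed envelopes and device programming.
3. Define the intention-to-treat set for the detraining comparison as every man allocated at week 12.
4. Analyse week-16 time to exhaustion adjusted for the week-12 value. This is worth doing even if the allocation stays at week 0.
5. Analyse the training phase by the two week-0 arms, so that men lost before week 12 still belong to a group.

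The four treatment sequences, visits and blinding do not change. The cost is a short amendment, a second envelope series and a second allocation step to keep concealed. Two limits remain. Week-16 comparisons across training arms, such as A versus D, stay exposed to loss during training. Loss or exclusion after week 12 is not helped by the change.
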